### Statistical analyses

2.13

The primary outcome is the symptom subscale of the HCT, with higher scores indicating greater symptom severity. Treatment efficacy will be evaluated based on the changes from baseline to Week 4.

Between-group differences will be analyzed using a linear mixed model (LMM). Fixed effects will include group (intervention vs. control), time (baseline, Week 4, and Week 8), and the group × time interaction, with the subject included as a random intercept. The LMM was selected because it appropriately accounts for within-subject correlation in repeated-measures data and allows the inclusion of participants with incomplete data under the maximum likelihood estimation framework, thereby reducing potential bias compared to complete-case analysis.

All efficacy analyses will be conducted according to the intention-to-treat (ITT) principle, including all randomized participants. Missing data will be handled under the assumption of missing at random (MAR) using maximum likelihood estimation within the LMM framework. In this study, reasons for dropout and the occurrence of adverse events will be collected whenever possible, and the MAR assumption was considered appropriate because missingness may be associated with observable factors such as previous measurements, treatment response, and adverse events. In addition, a per-protocol (PP) analysis reflecting adherence and major protocol violations will be performed to evaluate the consistency of the results.

The primary analysis will test the significance of the group × time interaction. A pre-specified contrast will be used to estimate the between-group difference in the mean change at Week 4. A decrease in score represents clinical improvement; therefore, a negative between-group difference in change (Δ intervention − Δ control) that is statistically significant will be interpreted as evidence of treatment efficacy.

Secondary outcomes (anger, depression, anxiety, HRV, and neurotic symptoms) will be analyzed using the same LMM framework. Variables without intermediate measurements, such as depression, anxiety, and HRV, can also be analyzed with LMM; in these cases, random slopes will be omitted and only random intercepts will be included. Contrasts can be specified to examine between-group differences at each time point. To control for multiplicity across secondary endpoints, the p-values will be adjusted using the Holm procedure.

Safety outcomes will be assessed descriptively based primarily on adverse events at Weeks 2, 4, and 8, without formal statistical testing. Individual participants with values outside the normal range will be recorded and reported on a case-by-case basis.

All statistical tests will be two-sided, and the significance level will be set at p < 0.05.

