### Sample size

2.5

This study is a confirmatory clinical trial designed to evaluate the efficacy of modified Ukgan-san compared with placebo in improving Hwabyung symptoms after 4 weeks of treatment. The primary outcome is the Hwabyung Comprehensive Test (HCT) score (16).

Because no previous pharmacological trials have used the HCT score, direct effect size estimates were unavailable. Therefore, the target effect size was determined based on prior randomized placebo-controlled trials of herbal medicines for emotional symptoms such as anxiety and depression, including studies using the Hamilton Anxiety Rating Scale (HAMA), Hamilton Depression Rating Scale (HAMD), and Depression Anxiety Stress Scales (DASS) (17–19). In these studies, standardized between-group effect sizes ranged from approximately d = 0.30 to 0.68, indicating moderate effects. Previous pharmacological studies in Hwabyung patients using the Hwabyung Symptom Scale (HB-S) reported minimal effect sizes (20, 21); however, these studies differed substantially in interventions, indications, and study design, and therefore were not considered appropriate references for the present trial.

Considering the expected therapeutic effects of modified Ukgan-san on neurotic symptoms and excitability, and conventional interpretations of clinically meaningful effects in anxiety and depression research, a target effect size of Cohen’s d = 0.60 was selected for this study.

Using a two-sided significance level of 0.05, statistical power of 80%, and an effect size of d = 0.60, the required sample size was calculated as 44 participants per group (total n = 88). Assuming a dropout rate of 15%, the final target sample size was set at 104 participants, with 52 participants allocated to each group.

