### Data collection and management

2.8

Assessments are scheduled at baseline (T1), mid-intervention (two weeks; T2), post-intervention (four weeks; T3), and follow-up (eight weeks; T4). Assessments include self-report ratings and heart rate variability (HRV) test. **Table 2** summarizes the assessment time points.

**Table 2 T2:** Study assessment points.

Assessments	Screening	T1	T2	T3	T4
SCID-HB	○				
CEAQ-s	○				
Blood test (Liver and Kidney Function Tests)	○			○	
Blood test (Thyroid Function Tests)	○				
Urine Test (u-HCG)	○				
Demographic Information	○				
HCT		○	○	○	○
STAXI-K		○	○	○	○
K-BDI, BAI		○		○	○
K-DERS		○	○	○	○
HRV		○		○	○
Adverse Events			○	○	○
Concomitant Medications	○		○	○	○
Medication Adherence			○	○	

T1, baseline; T2, mid-intervention; T3, post-intervention; T4, follow-up; SCID-HB, Structured Clinical Interview for Hwabyung; CEAQ-s, the Core Seven-Emotions Inventory Short Form; HCT, Hwabyung Comprehensive Test; STAXI-K, State-Trait Anger Expression Inventory-Korean Version; K-BDI, State–Trait Anger Expression Inventory-Korean Version; BAI, Beck Anxiety Inventory; K-DERS, Difficulties in Emotion Regulation Scale–Korean version; HRV test, Heart rate variability test.

To minimize participant dropout, sufficient information regarding the study schedule, assessment time points, and participant responsibilities will be provided at the start of the study. Reminder text messages will be sent prior to each assessment to notify participants of upcoming visits and survey schedules. Upon completion of the study, the participants will receive compensation that has been approved in advance.

If the participants withdraw from the study, no further assessments will be conducted. Data will be analyzed according to the intention-to-treat principle using linear mixed models, which account for missing data without explicit imputation. The reasons for discontinuation (e.g., personal circumstances, poor adherence, or adverse events) will be documented and recorded.

The research staff responsible for administering the questionnaire assessments and heart rate variability (HRV) measurements will remain blinded and will provide participants with procedural instructions that do not influence their responses. To improve data quality, missing items and abnormal responses will be checked when questionnaires are collected. In addition, key outcome variables will be double-checked when transferring participant data into an electronic case report form (eCRF).

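### The primary mixed model leaves the scheduled Week 2 HCT score out of its time factor, in conflict with Table 2 and with the random-slopes sentence, so it cannot use the only on-treatment score of participants who leave between Weeks 2 and 4

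*Protocol article*

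**What the plan says.** Section 2.8 sets the visits: "Assessments are scheduled at baseline (T1), mid-intervention (two weeks; T2), post-intervention (four weeks; T3), and follow-up (eight weeks; T4"). Table 2 marks the HCT, STAXI-K and K-DERS at all four of these visits, and K-BDI, BAI and HRV at T1, T3 and T4 only. Section 2.8 adds that nobody is assessed after withdrawing.

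Section 2.13 makes the change in the HCT symptom subscale from baseline to Week 4 the measure of efficacy and specifies the model: "Fixed effects will include group (intervention vs. control), time (baseline, Week 4, and Week 8), and the group × time interaction". The only random effect named is a subject intercept. Missing data are to be handled by maximum likelihood under missing at random (MAR), on the ground that "missingness may be associated with observable factors such as previous measurements, treatment response, and adverse events".

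For secondary outcomes, section 2.13 says: "Variables without intermediate measurements, such as depression, anxiety, and HRV, can also be analyzed with LMM", and that in those cases random slopes are dropped and only random intercepts kept.

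**The concern.** A likelihood-based analysis is protected against MAR dropout only to the extent that the data driving the dropout are in the model. For a participant who leaves between Weeks 2 and 4, the Week 2 score is the only post-baseline HCT value, and so the only HCT evidence of response. The model as listed does not contain it, yet the rationale for MAR leans on prior measurements and response.

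At stake is the primary contrast. If poor early responders leave one arm more than the other, the Week 4 difference is shifted, although the scores that could correct much of the shift were recorded. The random-slopes sentence adds a second problem: one section supports two readings of the model for the primary outcome, in a trial that calls itself confirmatory.

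**Working it through.** **1. The statements side by side.**

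| Source | Week 2 HCT | Random effects |
|---|---|---|
| Table 2 and section 2.8 | scheduled for all | not addressed |
| Section 2.13, primary model | absent from time factor | intercept only |
| Section 2.13, random-slopes sentence | implied to be used where measured | slopes implied where an intermediate visit exists |

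The second row conflicts with the first and the third.

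**2. The plan's own figures.** Section 2.5 states "a target effect size of Cohen’s d = 0.60 was selected for this study", with two-sided alpha 0.05 and 80% power. By the normal approximation, n per group = 2 × (1.960 + 0.842)² / 0.60² = 43.6, so 44, as stated. Allowing for 15% dropout, 44 / 0.85 = 51.8, so 52 per group and 104 in total, as stated.

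**3. How many could be affected.** 0.15 × 104 = 15.6, about 16 participants, if all dropout fell between Weeks 2 and 4. At 5% in that window, 0.05 × 104 = 5.2, about 5.

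**4. Simulation in SD units.** The documents give no HCT SD, correlations or dropout mechanism, so these are assumptions: SD 1 at each visit; true effect −0.30 at Week 2 and −0.60 at Weeks 4 and 8; correlation either compound symmetric (CS, 0.5 or 0.7) or decaying over time with 0.5 between baseline and Week 4; 15% overall leaving between Weeks 2 and 4, with logistic dependence (slope 2 per SD) on the change from baseline to Week 2. In the row where placebo non-responders leave, dropout is 25% on placebo and a random 5% on active. Both models have a random intercept. There were 200,000 participants per arm.

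| Dropout mechanism | Correlation | Without Week 2 | With Week 2 |
|---|---|---|---|
| Same in both arms | CS 0.5 | −0.597 | −0.597 |
| Same in both arms | decaying | −0.596 | −0.596 |
| Placebo non-responders leave | CS 0.5 | −0.521 | −0.601 |
| Placebo non-responders leave | decaying | −0.482 | −0.527 |
| Opposite by arm | CS 0.5 | −0.496 | −0.601 |
| Opposite by arm | decaying | −0.443 | −0.501 |

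CS 0.7 gave nearly the same estimates as CS 0.5. Bias without Week 2, as a share of 0.60: 0.079/0.60 = 13% and 0.104/0.60 = 17% under CS; 0.118/0.60 = 20% and 0.157/0.60 = 26% under decay.

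Rejection rates at 52 per arm, CS 0.5, 400 replicates (Monte Carlo error about 2 points), without and then with Week 2: same mechanism 0.81 and 0.81; placebo non-responders leave 0.64 and 0.79; opposite by arm 0.67 and 0.85.

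**5. Simulation in HCT points, varying how many leave in the window.** Assumed: true Week 4 difference −5; for example, change SD 8.5 (5/8.5 = 0.59, close to the planned d) and correlations of 0.45 to 0.75. Estimates from the three-time model, with ranges across the assumed inputs:

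| Dropout mechanism | 15% leave in window | 5% leave in window |
|---|---|---|
| Same in both arms | −4.96 | not run |
| Placebo non-responders leave | −4.27 to −4.42 | −4.75 |
| Placebo non-responders and active early responders leave | −3.53 to −3.75 | −4.55 |
| Active non-responders leave | −5.61 to −5.70 | −5.22 |

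At 15%, −4.28 is a bias of 0.72/5 = 14% and −3.53 is 1.47/5 = 29%; the smallest attenuation in the table, −4.42, is 0.58/5 = 12%. At 5%, the attenuation is 0.25/5 = 5% and 0.45/5 = 9%, about 10% in another run. The last row shows the effect exaggerated.

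**6. What restoring Week 2 achieves.** In the runs that gave −4.28 and −3.53, adding Week 2 under a random intercept gave −4.62 and −4.21. That recovers (4.62 − 4.28)/(5 − 4.28) = 47% and (4.21 − 3.53)/(5 − 3.53) = 46% of the bias. Adding it with an unstructured covariance gave −4.99 and −4.94.

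**The case against.** The strongest reply is that nothing shows a deliberate exclusion. The random-slopes sentence points the other way, so the time list may be a drafting slip. That stands, and it is why the point is put as an inconsistency to resolve.

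Several stronger readings are tempting, and the documents do not support them:

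- A reader might infer that the MAR assumption fails. MAR given baseline alone may still hold. What the listed model cannot do is use the post-baseline HCT scores on which the stated rationale would rely.
- A reader might infer that the primary result will be biased. That requires dropout to depend on Week 2 response differently by arm; with the same dependence in both arms there was no material bias.
- A reader might take 14 to 29% as the expected bias. Those figures put the whole 15% allowance into one two-week window. Section 2.5 gives an overall rate and no timing. Those who leave before Week 2 have no Week 2 score under any model, and those who leave after Week 4 already have the primary value.
- A reader might call this a complete-case analysis. Only leavers between Weeks 2 and 4 lose their on-treatment score, and their baseline still enters the likelihood.

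It is also fair to say that covariance structure is a separate matter: under compound symmetry, adding Week 2 alone removed the bias. The advice on covariance is therefore a preference that matters when correlations decay with time.

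**Conclusion.** The point holds as an internal inconsistency with a conditional consequence. Section 2.13 lists three times for an outcome that Table 2 schedules at four, and conflicts with its own random-slopes sentence. Read literally, the primary model cannot condition on the Week 2 score of participants who leave before Week 4.

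The size of the consequence rests on assumed SDs, correlations and dropout mechanisms. It runs from about zero (same mechanism in both arms), through about 5 to 10% of the effect (5% leaving in the window), to about 14 to 29% (all 15% leaving then). The direction can favour either arm. The endpoint, the Week 4 contrast and the sample size are not in question. Because differential dropout cannot be ruled out in advance and the repair uses scores already scheduled, the text should be corrected.

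**What to change.** In section 2.13, and in the analysis plan if there is one:

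- For HCT, STAXI-K and K-DERS, define time as baseline, Week 2, Week 4 and Week 8, categorical. Keep baseline, Week 4 and Week 8 for K-BDI, BAI and HRV.
- Keep the between-group difference in change at Week 4 as the primary contrast.
- Reconcile the random-slopes sentence with the primary model, so that one covariance specification applies to each outcome.
- Preferably use an unstructured within-subject covariance, since a random intercept removes only part of the bias when correlations are not compound symmetric.

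The cost is wording, plus a few more covariance parameters: four visits need 4 × 5/2 = 10, against 2 for a random intercept with residual variance. No new data or participants are needed. Recruitment has started, so the change should be dated and made before unblinding. It does not deal with dropout driven by adverse events, which the MAR rationale also cites and which neither version of the model contains.

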### Trial design

2.1

This study is a two-arm, randomized, triple-blind, placebo-controlled, parallel-group superiority trial. Participants will be randomly assigned in a 1:1 ratio to the experimental or the control group according to a randomization sequence generated using Microsoft Excel (Microsoft Corporation, Redmond, WA, USA). To ensure allocation concealment, the randomization sequence will not be disclosed to the enrollment personnel. After enrollment, the participants will be assigned to the experimental or control group according to a pre-generated randomization sequence.

The trial will comprise a 4-week intervention period followed by a 4-week follow-up period. Participants assigned to the experimental group will receive modified Ukgan-san for 4 weeks, whereas those assigned to the control group will receive a placebo identical in formulation but without the active ingredients for the same duration. Assessments will be conducted at four time points: baseline (T1), mid-treatment (T2), post-treatment (T3), and follow-up (T4).

This trial was registered with the Clinical Research Information Service (CRIS) the Republic of Korea (KCT0011347). This trial complies with the SPIRIT guidelines and will be conducted in accordance with the tenets of the Declaration of Helsinki. **Figure 1** presents a flowchart that provides an overview of the study design.

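### The primary HCT model fixes a random intercept only, while a later sentence presupposes random slopes; if the visits are not equally correlated, the Week 4 standard error is off in a direction that cannot be known in advance

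*Protocol article*

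**What the plan says.** All references are to the protocol article.

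- **Primary model (2.13 Statistical analyses).** A linear mixed model has fixed effects for group, "time (baseline, Week 4, and Week 8), and the group × time interaction", "with the subject included as a random intercept". No other covariance structure and no robust variance is stated. The confirmatory estimate is a single contrast: "A pre-specified contrast will be used to estimate the between-group difference in the mean change at Week 4".
- **Secondary outcomes (same section).** They "will be analyzed using the same LMM framework". For depression, anxiety and HRV, described as having no intermediate measurement, "in these cases, random slopes will be omitted and only random intercepts will be included".
- **Visits (2.8, Table 2).** HCT, STAXI-K and K-DERS are measured at baseline and Weeks 2, 4 and 8. K-BDI, BAI and HRV are measured at baseline and Weeks 4 and 8.
- **Treatment course (2.1 Trial design).** "The trial will comprise a 4-week intervention period followed by a 4-week follow-up period". Week 8 is therefore off treatment, yet it enters the same model as Week 4.

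**The concern.** A slope can be omitted for some outcomes only if other outcomes have one. By Table 2, the outcomes with an intermediate visit are HCT, STAXI-K and K-DERS, but the model the article describes has no slope at all. Two analysts could follow the section in good faith and fit different models to the primary outcome.

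The structure that is stated also matters. With a random intercept and the usual independent residuals, the standard error of the baseline-to-Week 4 change is pooled over every pair of visits, including Week 4 with Week 8, after treatment has stopped. If those pairs do not share one variance and one correlation, the p-value of the confirmatory test rests on the wrong standard error. Section 2.13 also relies on maximum likelihood under missing at random, and 2.8 ends assessment at withdrawal. With dropout, the estimate itself borrows through the assumed covariance.

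**Working it through.** **1. The plan's own figure.** Section 2.5 states: "Using a two-sided significance level of 0.05, statistical power of 80%, and an effect size of d = 0.60". The normal approximation gives n = 2(1.96 + 0.8416)²/0.60² = 43.6, so 44 per group. Then 44/0.85 = 51.8, so 52 per group and 104 in total. The sample size reproduces and is not at issue. It uses no visit correlation, so it gives no help with the covariance.

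**2. Formulas.** Assume complete data, time as categories, large samples, and true covariance S over t visits.

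- Random-intercept residual variance: [tr(S) − 1′S1/t]/(t − 1). The model's variance for the change is twice this.
- True variance of the change: v0 + v4 − 2·c04.
- SE ratio R = √(model variance / true variance).
- Actual two-sided type I error = 2[1 − Φ(1.96R)].
- Power, where 80% holds with the right SE: Φ(2.8016 − 1.96R).

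With equal SDs, R² = (1 − mean of all pairwise correlations)/(1 − r04).

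**3. Three visits (Weeks 0, 4, 8), the model as written.** The SDs and correlations are assumptions. Correlations are listed in the order 0–4, 0–8, 4–8.

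| Assumed truth | R² | R | Type I error | Power |
|---|---|---|---|---|
| Equal SDs, all correlations equal | 1 | 1.00 | 5.0% | 80% |
| Equal SDs, decay r, r², r with r = 0.3 | 1 + 0.3/3 = 1.100 | 1.049 | 4.0% | 77% |
| Same, r = 0.8 | 1 + 0.8/3 = 1.267 | 1.125 | 2.7% | 72% |
| SDs 8/9/10, 0.6/0.4/0.6 | 77.2/58.6 = 1.317 | 1.148 | about 2.5% | 71% |
| Equal SDs, 0.50/0.40/0.75 | 0.45/0.50 = 0.900 | 0.949 | 6.3% | – |
| SDs 7/10/10, 0.45/0.40/0.75 | 76.33/86 = 0.888 | 0.942 | 6.5% | – |

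Decay rows: the mean correlation is (2r + r²)/3, so R² = (1 − r)(3 + r)/[3(1 − r)] = 1 + r/3.

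Row with SDs 8/9/10: tr(S) = 245; the covariances are 43.2, 32 and 54, so 1′S1 = 245 + 2(129.2) = 503.4. The residual variance is (245 − 167.8)/2 = 38.6 and the model variance 77.2. The true variance is 64 + 81 − 86.4 = 58.6.

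**4. If Week 2 were included.** With equal SDs and correlation decaying in calendar time over Weeks 0, 2, 4 and 8, 4-week correlations of 0.3 to 0.8 give R of 0.98 to 1.02 and type I error of 5.4% to 4.5%.

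**5. Random slope instead.** Maximum-likelihood fits of a random intercept plus linear slope to three-visit truths gave R = 1.00 under decay, 1.09 with rising SDs (1/1.2/1.4 with 0.6/0.45/0.6), and 0.89 for 0.5/0.4/0.7. A slope does not remove the dependence on the unknown truth.

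**6. Unstructured covariance.** The contrast uses its own variance, v0 + v4 − 2·c04, so R = 1.00 in every row.

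**The case against.** The primary paragraph is explicit, and the slope remark sits in the secondary-outcome paragraph. The listed primary times contain no intermediate visit, so by the later sentence's own logic HCT would take a random intercept only. A random-intercept model is a common and accepted choice. The visit means are free, so the on/off-treatment course of the group means is fitted. Ordinary decay makes the three-visit test conservative. REML, degrees-of-freedom methods and fallback rules belong in a statistical analysis plan, which is not shown.

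Much of this stands. That HCT is meant to have random slopes is an inference; no sentence says so. The absence of REML or a degrees-of-freedom rule is not counted against the plan. But the consistent reading depends on Week 2 being outside the model, although HCT is measured then. Even confined to secondary outcomes, the sentence implies slopes for STAXI-K and K-DERS that the shared framework does not contain. And a conservative test costs power in a trial planned at 80%.

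Three stronger readings are tempting and not supported:

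- **That the type I error is inflated.** This requires, for example, post-baseline visits to correlate more closely with each other than baseline does with Week 4. That is plausible, but the article gives no figure for it.
- **That decay over four visits pushes the error above 7%.** Figures near that arise when decay is counted by visit number. At the actual unequal spacing the result is 4.5% to 5.4%.
- **That neither structure can suit an on/off-treatment course.** This is a judgement: a random slope fits three-visit decay exactly.

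**Conclusion.** The point holds at moderate size. The article fixes a restrictive covariance for its one confirmatory contrast and, in the same section, uses wording that presupposes a different one. If variances and correlations are not equal across visits, the Week 4 standard error is wrong, and the documents do not allow the direction to be predicted.

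In the three-visit illustrations, type I error runs from about 2.5% to 6.5%, and power falls to 71% to 77% where the standard error is too large. These figures rest wholly on assumed SDs and correlations, complete data and large samples. Other assumptions move them further: correlations 0.4/0.7/0.5 give R = √(0.4667/0.60) = 0.88 and 8.4%. There is no harm if variances and correlations are equal. With complete data only the standard error is affected, not the point estimate; with dropout the estimate also depends on the covariance. The finding does not show that the trial's test is invalid.

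**What to change.** For HCT and the other repeated outcomes, replace the random intercept with categorical visits and an unstructured within-subject covariance, fitted by REML with Kenward-Roger degrees of freedom. Name a simpler structure with a robust variance, to be used only if the model does not converge. Delete the random-slope sentence or reconcile it with the stated model, and say whether Week 2 is in the model for the outcomes measured then.

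The cost is wording and a few covariance parameters: 3·4/2 = 6 with three visits, or 4·5/2 = 10 with four. The planned 104 participants can support either, and the sample size does not change. Section 3.1 says recruitment has started, so the change should be documented before unblinding.

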### Randomization and allocation concealment

2.6

Participants will be allocated to either the experimental or control group in a 1:1 ratio using a simple randomization method. The randomization sequence will be generated and maintained using Microsoft Excel by an independent researcher ([name]) who is not involved in participant recruitment, assessment, or data analysis. Access to the randomization sequence will be restricted to the designated study coordinator, and investigators responsible for participant enrollment and assessment will not have access to the allocation sequence.

The manufacturer will prepare the study medication according to the randomization schedule. The prepared study medication will be labeled with a serial number in the UKS-AA-ZZZ format, provided to the principal investigator, and managed by the designated study pharmacist. In this labeling system, AA indicates the site number and ZZZ indicates the sequential number assigned to participants, beginning from 001.

The correspondence table linking the randomization schedule with the serial numbers of the study medication will be sealed and stored in a manner that allows verification of whether the seal has been broken, and access will be restricted to designated study management staff only. When a medication request is received from the investigator for a registered participant, the study pharmacist will assign the study medication sequentially to the participant and will record and manage the participant identification code on the study medication serial number log.

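### The test labelled primary is the overall group × time interaction, but the efficacy criterion and the sample size rest on the Week 4 difference alone

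*Protocol article*

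**What the plan says.** Section 2.13 (Statistical analyses) opens with the basis for judging efficacy on the HCT symptom subscale: "Treatment efficacy will be evaluated based on the changes from baseline to Week 4". It then specifies a linear mixed model with group, time and their interaction as fixed effects, time at three levels (baseline, Week 4, Week 8) and a random intercept for subject. Two paragraphs later it names the test: "The primary analysis will test the significance of the group × time interaction". The next sentence adds: "A pre-specified contrast will be used to estimate the between-group difference in the mean change at Week 4". The paragraph closes by saying that a significant group difference in change, in the direction of a larger fall in score on the intervention, will count as evidence of efficacy.

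Section 2.5 (Sample size) calls the trial confirmatory and gives its aim as evaluating the formula "compared with placebo in improving Hwabyung symptoms after 4 weeks of treatment". The calculation is a two-group comparison: "Using a two-sided significance level of 0.05, statistical power of 80%, and an effect size of d = 0.60", giving 44 per group. It is then inflated: "Assuming a dropout rate of 15%, the final target sample size was set at 104 participants", or 52 per group.

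**The concern.** The interaction in this model is not a Week 4 test. It asks whether the group difference changes anywhere across baseline, Week 4 and Week 8, so it gives the follow-up visit the same standing as the end of treatment. It also has no sign, whereas the efficacy sentence does. The test carrying the primary label is therefore not the one the efficacy criterion describes, nor the one the sample size was calculated for.

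The two tests can disagree. The interaction can be significant because of Week 8 alone. It can also miss significance when the Week 4 effect the trial was sized for is present and its contrast is significant. The section does not say what is concluded in either case. In a trial described as confirmatory, that should be settled before anyone sees the results.

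**Working it through.** **1. Reproduce the plan's sample size.** Inputs from section 2.5: two-sided α = 0.05, power 80%, d = 0.60, dropout 15%, 1:1 allocation.

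- n per group = 2 × ((1.960 + 0.842) / 0.60)² = 43.6, rounded up to 44. The t-test version gives 44.6, a rounding-level difference.
- 88 / 0.85 = 103.5, rounded up to 104.
- Power at 44 per group: 0.60 × √22 = 2.814; Φ(2.814 − 1.960) = 80.4% (79.5% by t-test).

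The stated figures come from a 1-df two-group formula. The powered test is the Week 4 comparison.

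**2. Degrees of freedom of the test named primary.** (2 − 1) × (3 − 1) = 2. The HCT is also scheduled at Week 2 in Table 2, but the time levels listed in section 2.13 leave that visit out, so 2 df is used here.

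**3. Power of the interaction.** Three inputs are assumptions, because the documents do not give them:

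- d is read in SDs of the change score; section 2.5 does not say which SD it means.
- The correlation between the Week 4 and Week 8 changes is 0.5. A random-intercept model implies this: the two changes share only the baseline residual, so the covariance is σ² and each variance is 2σ².
- The Week 8 effect d8 is varied from 0 to 0.60, with d4 = 0.60 and 44 per group.

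The noncentrality is (n/2) · d′R⁻¹d = 22 × (d4² − d4·d8 + d8²) / 0.75, referred to a chi-square on 2 df. The last column is from simulation (1,000,000 draws per scenario).

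| d4 | d8 | Noncentrality | Interaction power | Week 4 contrast power | Both significant |
|---|---|---|---|---|---|
| 0.60 | 0 | 10.56 | 83.7% | 80.4% | 76.1% |
| 0.60 | 0.15 | 8.58 | 74.9% | 80.4% | not run |
| 0.60 | 0.30 | 7.92 | 71.3% | 80.4% | 70.1% |
| 0.60 | 0.45 | 8.58 | 74.9% | 80.4% | 72.1% |
| 0.60 | 0.60 | 10.56 | 83.7% | 80.4% | 76.1% |
| 0 | 0.60 | 10.56 | 83.7% | 5.0% | 5.0% |

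At d8 = 0.30 the noncentrality equals that of the Week 4 contrast (22 × 0.36 = 7.92). Week 8 then adds no information and the second degree of freedom is pure loss. The two tests disagree in 11.5% of such trials: the contrast alone is significant in 10.3% and the interaction alone in 1.2%. For 80% power on the interaction in that scenario, 54 per group would be needed, or 128 with dropout (108 / 0.85 = 127.1).

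**4. Sensitivity to the correlation.** At 0.6 instead of 0.5, interaction power is 71–72% for d8 of 0.30 to 0.36, 81% at 0.60 and 89% at 0. An effect of 0.60 at Week 8 only gives 89% for the interaction and 5% for the contrast. The pattern is the same.

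**5. Type I error under each possible rule.** With no effect at either visit, each test alone rejects 5.0% of the time and both together 2.5%. Accepting either gives 5.0 + 5.0 − 2.5 = 7.5%.

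**The case against.** The best defence is that the intention is clear from context. Only the interaction is called primary, and the contrast is introduced as an estimate. A reader might infer that the protocol names two primary tests or has no success rule at all; the text supports neither. It gives one efficacy statement. That statement is directional and directly follows the Week 4 contrast, and an omnibus test has no sign with which to satisfy it. Read that way, an effect confined to Week 8 would not lead to an efficacy claim, however often the interaction were significant. The Week 4 contrast is also a component of the interaction, so the passage could be meant as one analysis reported through one contrast.

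A reader might also infer that type I error is inflated. The 7.5% needs a rule that either test suffices, and the section states no such rule. If the interaction acts as a gate, the rate is 2.5%; if the contrast decides, it is 5%.

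Nor does the mismatch always cost power. When the Week 8 effect is zero or equal to the Week 4 effect, the interaction slightly exceeds the planned 80%.

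All of this stands, and it narrows the point without removing it. The section does not restrict the interaction to its Week 4 term, and it brings in the Week 4 contrast separately. An analyst following the wording would report the 2-df test as the primary result. Test hierarchy can be left to an analysis plan, but here the article itself names a test that does not match its own criterion and sample size.

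**Conclusion.** The point holds as an inconsistency between the test labelled primary and everything else that defines success. The efficacy basis, the directional criterion and the 44 per group all belong to the 1-df Week 4 difference. The label sits on a 2-df test that includes a post-treatment visit, and whether that test must also be significant is unstated.

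Under the assumptions in the working (correlation 0.5, d in SDs of change, 44 completers per group, d = 0.60 at Week 4), the interaction has 71% to 84% power depending on the Week 8 effect, against 80% for the contrast. Requiring both gives 70% to 76%. With an effect of 0.60 at Week 8 only, the named primary test is significant in 84% of trials and the Week 4 contrast in 5%. The sample size itself is not at fault: it reproduces, and it is right for the Week 4 contrast.

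**What to change.** In section 2.13, replace the sentence naming the interaction as the primary test. State that the sole confirmatory test is the two-sided 5% test of the between-group difference in change from baseline to Week 4 in the HCT symptom score, estimated from the mixed model. State that the overall group × time interaction and the Week 8 contrast are supportive and play no part in declaring efficacy.

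The cost is one sentence in the protocol, carried into the analysis plan and the registry entry. The target of 104 and the stated 80% power then stand, and neither data collection nor participants are affected. Recruitment has started, so the change should be made and dated before unblinding.
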